### 2.6. Randomization and stratification

The patients are randomized 1:1 in a centralized block randomization manner to be allocated to either the same-day or the next-day arm. The randomization is stratified according to number of patient’s CIN risk factors (1 vs ≥ 2), chemotherapy setting (perioperative vs palliative), and interval of regimen (2-week vs 3-week). This clinical study is an open-label trial; both the investigator and the patient know which method is being administered.

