### 2.8. Outcome measures

Outcome measures are listed in Table 2.

**Table 2 T2:** Detailed descriptions of the endpoints.

Endpoints	Explanation
Duration of Gr4 CIN (cycle 1)	Duration (in d) of absolute neutrophil count (ANC) < 500/μL in the first chemotherapy cycle
Incidence of Gr 3–4 CIN (cycle 1)	Subjects with ANC < 1000/μL in the first chemotherapy cycle
Severity of CIN (cycle 1)	Minimum ANC level in the first chemotherapy cycle
Time to ANC recovery (cycle 1)	Time (in d) from day 1 of chemotherapy to ANC > 1000/μL after the nadir in the first chemotherapy cycle
Febrile neutropenia (FN) incidence (cycle 1–4)	Development of FN until 28 d after the end of cycle 4. FN is defined as an oral temperature rise to 38.3°C or higher or a fever of 38.0°C or higher that lasts for 1 h or more with an ANC <500/mm^3^ or with an ANC <1000/mm^3^ that is expected to decrease to <500/mm^3^ within 48 h
Incidence of CIN-related dose delay (cycle 1–4)	Delay of chemotherapy schedule due to development of CIN
Relative dose intensity (RDI) (cycle 1–4)	Dividing the total dose of chemotherapy (mg/m^2^) by the total administration period, and the value was expressed as a percentage based on the full dose intensity (Table 1)
Pegteograstim-related AEs (cycle 1–4)	Occurrence of bone pain and pneumonitis during cycles 1–4

AEs = adverse events, CIN = chemotherapy induced neutropenia, Gr = grade.

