### 2.10. Sample size calculation

The primary endpoint of the study is duration of Gr4 CIN. In prior studies using the next-day administration method, the duration of Gr4 CIN was approximately 2 to 2.5 days. Considering the non-inferiority margin of 0.6 days and equivalence margins of 1 to 2.1 days in previous studies,^[2,3]^ 0.6 days of Gr4 CIN duration was selected for the non-inferiority margin. In order to verify the non-inferiority of 0.6 days (standard deviation 1.4 days), a significance level of 5% and power of 80% were estimated. This resulted in the need for 136 patients, 68 per group. Adjusting for sample size by expecting a drop-out rate of 15% in each treatment group, we planned for enrollment of 160 total subjects, 80 subjects in each treatment group. The study subject registration period was assumed to be 2 years, and the follow-up period was assumed to be 3 months.

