### 2.11. Statistical analysis

The primary analysis is performed in the per-protocol (PP) set, considering the non-inferiority design. The per-protocol group is defined as patients who do not have any of these following significant deviations from the clinical trial protocol: Failure to administer the study drug (pegteograstim) within the scheduled period (same-day arm: within 4 hours, Next-day arm: 24–36 hours); Discontinuation of CBCs before < 50% of tests (on 3 or fewer days) or until ANC reaches > 500/μL, and; development of FN and treatment with additional filgrastim at the discretion of the investigator.

Demographics, clinical presentation, perioperative clinical findings, and laboratory values are summarized using descriptive statistics. Continuous variables are described by median values, and categorical variables are described by absolute numbers and percentages. *T* test is used for group comparison of continuous variables such as duration of Gr4 CIN, severity of CIN, and RDI. Chi-square test or Fisher exact test is used for group comparison of categorical variable values such as incidence of Gr 3 to 4 CIN (Cycle 1), FN, CIN-related dose delay, and pegteograstim-related AEs. Time to ANC recovery is analyzed by the method of Kaplan–Meier.

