## 3. Discussion

This study is a prospective randomized phase III study to verify the hypothesis that same-day administration of pegteograstim is non-inferior to next-day administration for 3 to 5 day chemotherapy regimens in which intensively myelosuppressive chemotherapy agents are administered on day 1. If the same-day method is non-inferior in regard to efficacy, patient convenience can be improved by removing the need for extension of hospitalization or revisit hospital to meet the next-day injection schedule.

The timing of administration of peg-GCSF is usually recommended to be 24 to 72 hours after completion of chemotherapy.^[1]^ If peg-GCSF is administered within 24 hours of completion of chemotherapy, myeloid progenitor cells are rapidly increased under stimulation of GCSF. The increased myeloid progenitor cells are depleted by myelosuppresive chemotherapeutic agents, thereby exacerbating CIN. This has been demonstrated in several clinical studies. In 2010, Burris et al^[3]^ showed that Gr4 ANC duration was shorter with the next-day administration (after 24 hours) than with the same-day administration (within 4 hours) method. The severity of CIN was also milder with the Next-day method. In addition, a large-scale retrospective cohort study showed that the same-day method was inferior to the next-day method for most evaluation factors.^[6]^

However, although the ASCO guidelines stipulate administration after 24 hours, these guidelines also recommend the same-day method for patients who have difficulties with next-day peg-GCSF administration.^[10]^ The reasoning behind this is that administration within 24 hours is better than not administering the peg-GCSF. Also, same-day administration showed improvement in Gr 4 CIN duration compared to next-day administration for ovarian cancers treated with the topotecan 5-day regimen. However, this was a subgroup analysis that did not reach statistical significance (same-day, 1.9 days; next-day, 2.4 days).^[3]^ In another retrospective study using 5-day DCF (Docetaxel, Cisplatin, and 5-FU) consisting of docetaxel and cisplatin on day 1, the same-day method showed superior outcomes in CIN incidence and FN prevention rates compared to the next-day method.^[8]^

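### The primary per-protocol set excludes patients who develop febrile neutropenia and receive filgrastim, so it selects on the outcome and can shrink a real same-day disadvantage toward non-inferiority

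*Protocol article*

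**What the plan says.** Section 2.11 of the protocol article fixes the primary population: "The primary analysis is performed in the per-protocol (PP) set, considering the non-inferiority design". It then defines that set by the absence of three kinds of significant deviation: pegteograstim given outside its time window, too few blood counts, and "development of FN and treatment with additional filgrastim at the discretion of the investigator".

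The primary endpoint (Table 2, section 2.8) is "Duration (in d) of absolute neutrophil count (ANC) < 500/μL in the first chemotherapy cycle". The same table defines FN as fever "with an ANC <500/mm^3^ or with an ANC <1000/mm^3^ that is expected to decrease to <500/mm^3^ within 48 h". FN is also a secondary endpoint, followed well past cycle 1: "Development of FN until 28 d after the end of cycle 4". Section 2.6 states that the trial is open label, so that "both the investigator and the patient know which method is being administered".

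No other section of the article says how patients with FN and filgrastim enter the primary analysis. The drop-out criteria in section 2.9 are withdrawal of consent and pregnancy only.

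**The concern.** A per-protocol set is normally restricted by departures from the protocol, such as a late injection or missing blood counts. The third criterion is different. A patient injected on time with a complete series of counts is removed because neutropenia became severe enough to cause fever and be treated. The exclusion is a consequence of the variable under test.

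The non-inferiority test must guard against same-day dosing being worse. Section 3 reports that direction from an earlier trial: "Gr4 ANC duration was shorter with the next-day administration (after 24 hours) than with the same-day administration (within 4 hours) method". If it holds here, more same-day patients would be expected to meet the criterion and leave the same-day mean. The harm that the trial looks for would then partly remove itself from the comparison.

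Two features add to this. Filgrastim is given at the discretion of an investigator who knows the arm, so membership of the primary set can depend on allocation through that decision as well. And the criterion names no cycle, so FN treated in cycle 3 could delete a valid cycle 1 measurement.

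**Working it through.** **The plan's own figure.** Section 2.10 gives a margin of 0.6 days, SD 1.4 days, significance level 5%, power 80%. With a true difference of 0 and a one-sided 5% level:

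n per group = 2 × 1.4² × (1.645 + 0.842)² / 0.6² ≈ 67.3, so 68; and 68 / (1 − 0.15) = 80.

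Both figures reproduce. A one-sided 2.5% level would need 86 per group, so one-sided 5% is used below.

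**Inputs.** From the article: margin 0.6 days; next-day mean 2.0 days, the lower end of the range in section 2.10 ("the duration of Gr4 CIN was approximately 2 to 2.5 days"); 68 per arm before exclusion. Assumed, because the article gives no rate: the proportion f excluded in each arm, and the mean grade 4 duration D of excluded patients (4 or 5 days in both arms). The true difference is set at the margin (same-day mean 2.6), where a valid test declares non-inferiority about 5% of the time.

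**Formula.** Mean of those who remain = (overall mean − f × D) / (1 − f).

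Example, D = 5, exclusion 15% same-day v 5% next-day:
- Next-day: (2.0 − 0.05 × 5) / 0.95 = 1.842
- Same-day: (2.6 − 0.15 × 5) / 0.85 = 2.176
- Per-protocol difference: 0.334 days, against a true 0.6

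**Results.** False non-inferiority rates are simulated: Poisson durations within excluded and retained groups, t-based upper one-sided 95% limit below 0.6. They move by about one percentage point between runs.

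| Excluded, same-day v next-day | Difference left, D = 4 | False non-inferiority, D = 4 | Difference left, D = 5 | False non-inferiority, D = 5 |
|---|---|---|---|---|
| none (all kept) | 0.60 | about 5% | 0.60 | about 5% |
| 5% v 5% | 0.63 | about 4% | 0.63 | about 4% |
| 10% v 5% | 0.55 | about 8% | 0.49 | about 11% |
| 15% v 10% | 0.58 | about 7% | 0.51 | about 11% |
| 15% v 5% | 0.46 | about 13% | 0.33 | about 27% |
| 20% v 10% | 0.47 | about 12% | 0.33 | about 27% |

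**Second model.** Gamma durations with SD exactly 1.4, 80 per arm, next-day mean 2.0 or 2.5, and a probability of exclusion that rises with duration:
- Same exclusion rule in both arms (about 6–22% of next-day and 8–30% of same-day patients excluded): false non-inferiority 5.4% to about 10%.
- Odds of exclusion also 1.65 times higher in the same-day arm: about 8% to 19%.
- Exclusion unrelated to duration: 5.1%, so no bias.

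Both models show that the inflation comes from exclusion that is linked to duration and more frequent in the same-day arm.

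**The case against.** The strongest defence is that filgrastim can itself shorten the time below 500/μL. Treated patients no longer show the effect of pegteograstim timing alone, and excluding them limits that confounding. This is a plausible motive and it stands as a reason to handle these patients with care. It does not justify deletion, which replaces a possibly shortened duration with none at all and does so more often in the arm that performs worse.

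Four stronger readings are tempting, and the article does not support them.

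- **That the result is always pushed toward non-inferiority.** With equal exclusion the difference moves slightly the other way (0.63 days). Section 3 also cites multi-day regimens in which same-day dosing looked better, though one was a non-significant subgroup (1.9 v 2.4 days) and the other a retrospective study.
- **That error is inflated to around 80%.** A figure of 82% against 6% can be produced with 29% v 5% excluded, 4 days for excluded patients and 1.5 days for everyone else in both arms. That places the whole 0.6-day effect in the excluded patients. It also gives a next-day mean of 0.05 × 4 + 0.95 × 1.5 = 1.625 days, below the article's 2 to 2.5, and an exclusion rate nearly twice the 15% drop-out allowance.
- **That all the worst outcomes are deleted.** FN and added filgrastim are both required. Long neutropenia without fever stays in, and FN can be met on an expected fall, so some excluded patients may have few grade 4 days.
- **That no other analysis of the primary endpoint exists.** The article is silent on this, and a full protocol or SAP may name one. A companion analysis would still not change which analysis is primary.

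**Conclusion.** The criterion is unsound as written and should be changed. It conditions the primary analysis on an event defined by the endpoint's own threshold and on an unblinded treatment decision, with no limit to the cycle in which the endpoint is measured. Calling the population per-protocol on account of the non-inferiority design does not justify it: that population is chosen so that non-adherence does not blur a real difference, whereas this exclusion can blur one.

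The direction is conditional: toward non-inferiority if same-day dosing is truly worse and therefore loses more patients. The existence of the problem is certain from the text, but its size is not. The 7–13% and 11–27% ranges rest on assumed exclusion rates, assumed durations and Poisson spread. The milder model gives 5.4% to about 10% under one exclusion rule for both arms. These are possible inflations of a nominal 5%, not forecasts.

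**What to change.** 1. Delete the criterion on FN with additional filgrastim from the per-protocol definition in section 2.11. Keep the criteria on injection timing and blood counts.
2. State that these patients stay in the primary analysis with their observed number of days with ANC below 500/μL in cycle 1.
3. Pre-specify a sensitivity analysis in which patients given filgrastim for FN in cycle 1 receive a conservative (long) duration, fixed in advance by the same rule in both arms. Require the non-inferiority conclusion to be consistent with it.

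The cost is a change of wording and one added analysis before database lock. No new data are needed, because section 2.7 already continues daily counts until the ANC recovers to 1000/mm³, and the treatment of FN is untouched.

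The downside is that observed days may be shortened by filgrastim, which could itself favour the arm that receives more of it. The sensitivity analysis bounds this but does not remove it. A very long assigned value, such as the longest in the trial, may overcorrect and is not guaranteed to be neutral between arms.

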### 2.3. Participants

Patients with adjuvant/neoadjuvant or first-line palliative chemotherapy with regimen containing an intensively myleosuppressive agent on day 1 are enrolled.

Enrollment criteria are: Patients with histologically confirmed malignancy who are scheduled for adjuvant/neoadjuvnat or first-line palliative chemotherapy with multi-day combination regimens. These regimens include mFOLFIRINOX for Pancreatic cancer, ECb and EP for Small cell carcinoma, Neuroendocrine carcinoma, and FOLFOX and FOLFIRI for colorectal cancer. Detailed contents of these regimen are described in Table 1. The patients receiving FOLFOX and FOLFIRI combination therapies with targeted agents such as cetuximab or bevacizumab are also included, and those receiving atezolizumab in addition to the ECb and EP regimens for small cell lung carcinoma are also eligible; Patients with 1 or more risk factors for CIN: 65 years of age or older, previous history of chemotherapy or radiation therapy, recent surgery and open wounds, liver dysfunction with total bilirubin > 2.0 mg/dL, renal dysfunction with creatinine clearance < 50 mL/minutes. An exception is that patients on the mFOLFIRINOX regimen can be enrolled without CIN risk factors due to the high-risk for CIN of this regimen; Patients who are scheduled to receive 100% dose of chemotherapy; Patients between the ages of 19 and 75; Patients with Eastern Cooperative Oncology Group performance status 0 to 1; Patients with adequate bone marrow function for chemotherapy [absolute neutrophil count (ANC) ≥ 1500/μL], (platelets ≥ 100,000/μL, and hemoglobin ≥ 9.0 g/L), adequate renal function (creatinine clearance ≥ 40 mL/minutes), adequate liver function [total bilirubin in the blood < 1.5 × upper limit normal (ULN), alanine aminotransferase or aspartate aminotransferase  < 3.0 × ULN. The alanine aminotransferase or aspartate aminotransferase value must be ≤ 5.0 × ULN in patients with documented disease metastases to the liver); Patients who agreed to participate in the study.

**Table 1 T1:** Chemotherapy regimens.

Cancer type	Regimen		Day
Pancreatic cancer	mFOLFIRINOX		Every 2 wk
	5-FU	1200 mg/m^2^ IV continuous infusion	d 1–2
	Oxaliplatin	85 mg/m^2^ IV	d 1
	Irinotecan	150 mg/m2 IV	d 1
Small cell carcinoma, Neuroendocrine carcinoma	EP*		Every 3 wk
	Etoposide	100 mg/m^2^ IV	d 1–3
	Cisplatin	70 mg/m^2^ IV	d 1
Small cell carcinoma, neuroendocrine carcinoma	ECb*		Every 3 wk
	Etoposide	100 mg/m^2^ IV	d 1–3

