-Duration of Gr4 CIN (cycle 1): duration (in days) of ANC < 500/μL in the first chemotherapy cycle.-Incidence of Gr 3 to 4 CIN (cycle 1): subjects with ANC < 1000/μL in the first chemotherapy cycle.-Severity of CIN (cycle 1): minimum ANC level in the first chemotherapy cycle.-Time to ANC recovery (cycle 1): time (in days) from day 1 of chemotherapy to ANC > 1000/μL after the nadir in the first chemotherapy cycle.-FN incidence (cycle 1–4): development of FN until 28 days after the end of cycle 4. FN is defined as an oral temperature rise to 38.3°C or higher or a fever of 38.0°C or higher that lasts for 1 hour or more with an ANC <500/mm^3^ or with an ANC <1000/mm^3^ that is expected to decrease to <500/mm^3^ within 48 hours.-Incidence of CIN-related dose delay (cycle 1–4).-Relative dose intensity (RDI) (cycle 1–4): RDI is calculated by dividing the total dose of chemotherapy (mg/m^2^) by the total administration period, and the value was expressed as a percentage based on the full dose intensity (Table 1).-Pegteograstim-related AEs (cycle 1–4): the occurrence of bone pain and pneumonitis during cycles 1 to 4.

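### The t tests named for Gr4 duration and minimum ANC are valid, but they forgo precision that adjustment for entry ANC could give; the size of the gain is unknown

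*Protocol article*

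**What the plan says.** All references are to the protocol article.

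- **Entry value.** Section 2.3 requires adequate marrow function, including "absolute neutrophil count (ANC) ≥ 1500/μL". An ANC before treatment must therefore be known for each patient enrolled. The article gives no timing for this measurement.
- **Outcomes.** Table 2 in 2.8 defines the primary endpoint as "Duration (in d) of absolute neutrophil count (ANC) < 500/μL in the first chemotherapy cycle" and severity of CIN as "Minimum ANC level in the first chemotherapy cycle". Both are summaries of the ANC course after treatment.
- **Analysis.** Section 2.11 assigns a t "test is used for group comparison of continuous variables such as duration of Gr4 CIN, severity of CIN, and RDI". It names no covariate for these comparisons.
- **Randomisation.** Section 2.6 stratifies by number of CIN risk factors, chemotherapy setting and regimen interval. Entry ANC is not a stratum, and it is not among the risk factors listed in 2.3.
- **Sample size.** Section 2.10 states that "0.6 days of Gr4 CIN duration was selected for the non-inferiority margin". With an SD of 1.4 days, a 5% significance level and 80% power it reaches 68 per group, or 80 per group after 15% drop-out.

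**The concern.** When the baseline value of the outcome variable is already at hand, adjusting for it is usually the cheapest way to narrow a confidence interval. The variation in Gr4 duration or nadir depth that entry ANC predicts, if there is any, stays in the error term of a t test. The interval set against the 0.6-day margin is then wider than it needs to be, and the comparison of nadirs is less sensitive to a disadvantage of same-day dosing.

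Chance imbalance is a second, smaller consideration. Randomisation balances entry ANC in expectation, but stratification does not control it directly. If the arms differ by chance, the estimated difference moves in proportion to the slope of the outcome on entry ANC.

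The design has little reserve: 68 evaluable patients per group give just 80% power when the true difference is zero.

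**Working it through.** **Inputs from 2.10:** margin 0.6 days, SD 1.4 days, 5% significance level, 80% power, 68 per group, 15% drop-out. **Assumptions:** a true difference of 0; one-sided 5% (the article does not state sidedness); and rho, the within-arm correlation of entry ANC with the outcome, for which the article gives no figure.

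**Step 1. Reproduce the plan's figure.**

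n per group = 2 × SD² × (z₀.₉₅ + z₀.₈₀)² / margin² = 2 × 1.96 × (1.645 + 0.842)² / 0.36 = 67.3, rounded up to 68. The total is 136, and 136 / 0.85 = 160. Both stated totals are reproduced. At one-sided 2.5% the same formula gives 86 per group, 172 in total and 203 enrolled, which does not match. So the plan's calculation is for an unadjusted comparison at one-sided 5%.

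**Step 2. Effect of adjustment on Gr4 duration.**

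Adjustment multiplies the residual variance by (1 − rho²), so the residual SD is 1.4 × √(1 − rho²). Power is from the noncentral t distribution with noncentrality 0.6 / (residual SD × √(2/68)), and one degree of freedom is charged for the covariate. The half-width is 1.645 × residual SD × √(2/68).

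| rho (assumed) | variance factor | residual SD (days) | power | half-width (days) |
|---|---|---|---|---|
| unadjusted | 1.00 | 1.400 | 80.0% | 0.395 |
| 0.1 | 0.99 | 1.393 | 80.3% | 0.393 |
| 0.2 | 0.96 | 1.372 | 81.4% | 0.387 |
| 0.3 | 0.91 | 1.336 | 83.2% | 0.377 |
| 0.4 | 0.84 | 1.283 | 85.7% | 0.362 |
| 0.5 | 0.75 | 1.212 | 89.0% | 0.342 |

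A normal approximation gives values about 0.3 points higher with the same pattern. Estimating the slope costs roughly a further 0.3 points, which cancels the gain at rho 0.1. A gain of 5 points needs rho of about 0.38. At rho 0.5 the gain equals that of 68 / 0.75 = about 91 per group unadjusted.

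**Step 3. Effect of a chance imbalance.**

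If the arm means of entry ANC differ by one standard error of that difference, the unadjusted estimate shifts by rho × 1.4 × √(2/68) = rho × 0.240 days. That is 0.07 days at rho 0.3 and 0.12 days at rho 0.5, against a margin of 0.6 days. The t test's standard error already allows for such shifts.

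**Step 4. Minimum ANC.**

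The article gives no effect size or power for this endpoint, so only the relative effect can be shown. For a comparison that happened to have 80% power unadjusted at two-sided 5%, adjusted power is Φ(2.8016 / √(1 − rho²) − 1.96), or 83.6% at rho 0.3 and 89.9% at rho 0.5. The 80% starting point is illustrative.

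**The case against.** The strongest reply is that nothing here is wrong. Under randomisation the unadjusted t test is a valid comparison. Step 1 shows that the sample size was built on it, so on the plan's own assumptions the trial delivers the 80% power it claims. **This stands**, and it limits the point to a recommendation.

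The second reply is that no correlation is documented and that it may be weak for the primary endpoint. Gr4 duration is a short day count with a floor at zero; 2.10 cites about 2 to 2.5 days in earlier studies. Entry ANC is cut off below at 1500/μL. The population mixes five regimens, two cycle lengths and two treatment settings, which may drive variation that entry ANC does not predict. **This also stands**: at rho 0.1 to 0.3 the primary analysis gains about 3 points of power at most. The case is better for minimum ANC, a continuous value on the same scale as the covariate.

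The third reply is that covariates are commonly left to an SAP, which is not shown. This carries less weight, because 2.11 is not silent: it names the t test for these two outcomes, and a later adjusted model would depart from the published text.

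A reader might infer more than the article supports:

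- *That precision is in fact being lost.* This needs a correlation of useful size, and none is given.
- *That entry ANC is left unbalanced and any imbalance carries over in full.* Randomisation balances it in expectation, and an imbalance carries over only through the outcome's slope on it.
- *That the trial is underpowered without adjustment.* The calculation in 2.10 is consistent with the test in 2.11.

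**Conclusion.** The point holds as a possible improvement in efficiency, not as an error or a contradiction. Section 2.11 fixes a test without covariates for two outcomes derived from ANC, although an entry ANC must exist for each patient. Prespecified adjustment would raise power for the primary comparison from 80.0% to between about 81% and 89% for rho from 0.2 to 0.5, and would give essentially nothing at rho of about 0.1 or less. This rests on the plan's margin, SD and 68 per group, on one-sided 5% and a true difference of 0, and on an assumed rho. The lower part of the range seems more likely for Gr4 duration, and a worthwhile gain is more plausible for minimum ANC. The change is still worth making, because it costs very little and the covariate has to be chosen before outcome data are seen.

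**What to change.** In 2.11, replace the unadjusted t test for duration of Gr4 CIN and for minimum ANC with a prespecified linear model containing arm and baseline ANC, defined as the last value before cycle 1 chemotherapy. For the primary endpoint, compare the upper confidence limit of the adjusted mean difference in days (same-day minus next-day) with 0.6. Keep the unadjusted difference as a sensitivity analysis, so that the result on which the sample size rests is still reported.

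The cost is one degree of freedom, a sentence of analysis text, and making sure that the eligibility ANC is recorded as a number on the case report form and not only as a criterion met. No further patients or visits are needed, and the sample size need not change.

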## 2. Methods

### 2.1. Study design

This study is a randomized, multicenter, parallel, open-label, phase III study. This study is designed to test the non-inferiority of same-day to next-day administration of pegteograstim (Fig. 1).

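### The primary T test on Gr4 CIN duration makes no use of the three stratification factors; adjusting for them would tighten the interval at almost no cost

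*Protocol article*

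**What the plan says.** Section 2.10 of the protocol article states: "The primary endpoint of the study is duration of Gr4 CIN". Section 2.1 gives the aim: "This study is designed to test the non-inferiority of same-day to next-day administration of pegteograstim". Section 2.10 fixes the margin ("0.6 days of Gr4 CIN duration was selected for the non-inferiority margin") and the sizing inputs ("In order to verify the non-inferiority of 0.6 days (standard deviation 1.4 days"), and adds that "a significance level of 5% and power of 80% were estimated". The result is 68 evaluable patients per arm, raised to 80 for 15% drop-out.

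Section 2.6 stratifies the 1:1 block randomization by number of "CIN risk factors (1 vs ≥ 2), chemotherapy setting (perioperative vs palliative), and interval of regimen (2-week vs 3-week").

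Section 2.11 gives the method for the primary endpoint in one sentence shared with two secondary endpoints: a T "test is used for group comparison of continuous variables such as duration of Gr4 CIN, severity of CIN, and RDI". It names no stratification factor or other covariate. It does say that the per-protocol set is primary because the design is non-inferiority.

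**The concern.** Stratified randomization balances the arms on the chosen factors. If those factors predict the outcome, this balance makes the estimated difference less variable than a two-sample T test assumes. The T test leaves the between-stratum variation in its standard error, so its interval is too wide. Putting the factors in the model removes that variation.

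What is at stake is efficiency. The trial is sized at 80% power with no reserve, and its conclusion depends on whether one confidence limit falls below 0.6 days. An interval wider than necessary raises the chance that a truly non-inferior same-day schedule fails to show it.

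**Working it through.** **Inputs.** From section 2.10: margin 0.6 days, SD 1.4 days, significance level 5%, power 80%, 68 per arm, drop-out 15%. Not in the document: the true difference (taken as 0), the sidedness of the 5%, and R², the share of outcome variance explained by the covariates (taken as 5% to 30%).

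**Step 1: reproduce the stated size.**
n per arm = 2 × SD² × (z₁₋α + z₁₋β)² / margin².
- One-sided 5%: 2 × 1.96 × (1.645 + 0.842)² / 0.36 = 67.3, so 68. Drop-out: 68 / 0.85 = 80 per arm, 160 in total. This matches the plan.
- One-sided 2.5%: 2 × 1.96 × (1.960 + 0.842)² / 0.36 = 85.5, so 86. This does not match.

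The plan's size is therefore an unadjusted comparison against the 0.6-day margin at one-sided 5% with true difference 0.

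**Step 2: planned power of the unadjusted test.**
SE = 1.4 × √(2/68) = 0.240 days. Power = Φ(0.6/0.240 − 1.645) = Φ(0.854) = 80.3%.

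**Step 3: adjusted analysis.** The residual SD is 1.4 × √(1 − R²), and power = Φ(0.6 / (residual SD × √(2/68)) − 1.645).

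| Assumed R² | Residual SD (days) | SE (days) | Power, adjusted |
|---|---|---|---|
| 0 | 1.400 | 0.240 | 80.3% |
| 0.05 | 1.365 | 0.234 | 82.1% |
| 0.10 | 1.328 | 0.228 | 83.9% |
| 0.20 | 1.252 | 0.215 | 87.5% |
| 0.30 | 1.171 | 0.201 | 91.0% |

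The loss of three degrees of freedom out of about 134 is negligible.

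**Step 4: how the unadjusted test behaves if the strata are prognostic.** Suppose R² comes wholly from the stratification factors and the arms are balanced on them. The estimate then has the smaller SE, while the T test still uses 0.240. Its error rate when the true difference is 0.6 days is Φ(−1.645/√(1 − R²)). Its power at a true difference of 0 is Φ(0.854/√(1 − R²)).

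| Assumed R² | One-sided error at the margin (nominal 0.05) | Power, unadjusted | Power, adjusted |
|---|---|---|---|
| 0.05 | 0.0457 | 81.0% | 82.1% |
| 0.10 | 0.0415 | 81.6% | 83.9% |
| 0.20 | 0.0330 | 83.0% | 87.5% |
| 0.30 | 0.0247 | 84.6% | 91.0% |

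The unadjusted test stays below its nominal error and at or above 80% power. Against its actual power, adjustment adds about 1 to 6 points over this range. Against the planned 80.3%, it adds about 2 to 11.

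**The case against.** The strongest reply is that the trial was sized on an unadjusted SD and an unadjusted comparison, so the T test delivers what was planned, and ignoring the strata makes a false claim of non-inferiority less likely. Adjustment is then a gain over the plan and not the repair of an error. All of this stands. So does the point that the gain depends on an R² the document does not supply: at 5% it is small, and if the factors are not prognostic there is none. What remains is that the method named is less efficient than one using information the trial already holds.

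Four stronger readings are tempting and are not supported.

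- *The margin is never tested.* Section 2.11 does not write out the decision rule or its level. But sections 1.2, 2.1 and 2.10 fix non-inferiority at 0.6 days, and the sample size reproduces as a margin test. A T test can be run against a shifted null or reported as a confidence limit. Nothing says that a non-significant difference would be taken as non-inferiority.
- *Leaving out regimen departs from the design.* Regimen is not a randomization factor, and the standard error already reflects chance imbalance in it.
- *The strata are known drivers of CIN.* Section 2.6 gives no reason for choosing them. Section 2.3 describes only the patient-level items as CIN risk factors, not setting or interval. Their prognostic value is therefore an assumption here.
- *The summary contradicts the test.* The sentence "Continuous variables are described by median values" belongs to the descriptive statistics and does not alter the comparison of means.

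**Conclusion.** The point holds as a low-cost improvement. Section 2.11 assigns an unadjusted test to the primary endpoint of a trial randomized within strata. If the strata are prognostic, the interval is too wide, the test is conservative and some power is given up. For covariates explaining 5% to 30% of the variance, adjusted power is 82% to 91%, against 80% planned.

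These figures rest on 68 evaluable patients per arm, SD 1.4 days, a true difference of 0, one-sided 5% and a normal approximation. R² is assumed throughout. A reader should not infer that the planned analysis is invalid, that it inflates the error rate or that the trial is underpowered on its own assumptions.

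**What to change.** State the primary analysis as the same-day minus next-day difference in mean Gr4 days in cycle 1, from a linear model with arm, number of risk factors, chemotherapy setting and cycle interval, with robust standard errors. Conclude non-inferiority if the upper limit of the one-sided 95% confidence interval is below 0.6 days. That level should be written down, because it is the one 68 per arm supports.

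Two details need settling in the same text:

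- **Patients with no risk factor.** Section 2.3 admits mFOLFIRINOX patients without any CIN risk factor, but the stratum is 1 versus 2 or more. Code them in the model as they were handled at randomization, and say so.
- **Regimen, optional.** Section 2.3 treats mFOLFIRINOX as high-risk, while the other 2-week regimens require a risk factor. A prespecified three-level term (mFOLFIRINOX, FOLFOX/FOLFIRI, EP/ECb) could capture this. It should replace interval, because EP/ECb are the 3-week regimens and the term already carries that contrast.

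Keep the T-test interval as a sensitivity analysis. The cost is wording, fixed before the data are analysed. The stratification factors are needed to randomize each patient and regimen is known at enrolment, so nothing new is collected and the sample size is unchanged.
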